### Specific objectives (as specified during ethics submission)

The primary objective of the intervention is to achieve a weight reduction of ≥ 10% and an HbA1c level of <6.5% without pharmacotherapy, with the ultimate goal of achieving diabetes remission. The secondary objective of the intervention is to evaluate its effect on other aspects of diabetes outcomes, including mental health (anxiety and depression), comorbidities (hypertension and dyslipidaemia), diabetes-related complications (nephropathy), and biochemical parameters (serum lipids, liver function tests, and kidney function tests).

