### Setting and eligibility criteria

The proposed study will be conducted at the Freedom from Diabetes Clinic, which operates on an online subscription-based model of 1-year duration for the management of diabetes (intervention group). Additionally, the study will include participants from two private clinics in Pune and Ahmedabad (India) (Control Group), which provide standard medical care based on established guidelines for individuals with diabetes. All individuals with T2D who enrol in these centres between March and August 2024 and meet the eligibility criteria will be recruited for this study Table 1.

**Table 1 pone.0306394.t001:** Eligibility criteria for the DiRemI study.

Inclusion Criteria	Exclusion Criteria
Age between 30 and 70 years	Pancreatitis or drug-induced diabetes (Steroids)
Confirmed diagnosis of type 2 diabetes, which may be managed with oral hypoglycemic agents, insulin, Ayurvedic antidiabetic medications, or have an HbA1c level of ≥ 48 mmol/mol (6.5%) with or without medication	Other types of diabetes (type 1 diabetes mellitus, diabetes insipidus, maturity-onset diabetes of the young, latent autoimmune diabetes in adults, or Gestational Diabetes)
Body mass index (BMI) between 25 kg/m^2^ and 35 kg/m^2^	Advanced complications related to nephropathy (eGFR<30 mL/min/1.73 m^2^, urine microalbumin >1000 mg), retinopathy (severe non-proliferative diabetic retinopathy and proliferative diabetic retinopathy), neuropathy (peripheral artery disease or diabetic neuropathy resulting in complete numbness and loss of sensation, amputations, ulcers, foot deformities, Charcot’s foot)
Duration of type 2 diabetes less than 15 years	History of heart attack, cardiac arrhythmia, bypass or stent placement surgery, ischemic heart disease, angina (class II or III), myocardial infarction within the previous 6 months, reported ejection fraction <40%, abnormal ECG, and positive stress test results (moderate or severe)
Ready to provide written informed consent	Known history of cancer
Agree to undergo the examination, lifestyle intervention program, and post-program evaluation	Pregnant and lactating women
Well-oriented in time, space, and as a person	Patients who have required hospitalization for any diabetes-related complications in the last 6 months or for depression or are on antipsychotic drugs

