#### Biochemical

Data on the following biochemical tests will be collected from lab reports done at Government certified- NABL (National Accreditation Board for Testing and Calibration Laboratories, Govt. of India) labs; Primary: HbA1c, fasting blood sugar (FBS), postprandial blood sugar; secondary: lipid profile (total cholesterol, HDL, LDL, and VLDL), thyroid profile (thyroid-stimulating hormone), fasting insulin, serum creatinine levels, eGFR, urine microalbumin, liver function parameters, high sensitivity C-reactive protein (hs-CRP), C-peptide, Vitamin D, and Vitamin B12 will be collected based on availability in the submitted reports. Homeostatic model assessment of insulin resistance (HOMA-IR) and homeostatic model assessment of beta cell function (HOMA-B) will be calculated using standard formulas to assess insulin resistance and beta-cell function, respectively [19].

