#### Dietary modifications

Dietary intervention is focused on a plant-based diet, individualised based on the BMI and associated medical conditions of the participants. The four distinct phases of dietary intervention are adjustment, accelerated weight loss, muscle building, and maintenance. As part of the dietary intervention, participants are primarily introduced to consuming greens, lentil-based food items, sprouts, and vegetable salads. Soaked nuts such as walnuts, almonds, seeds, and fruits are also recommended for consumption, based on individual blood sugar levels. Sample diet charts are included in the supplementary file (S2 Appendix).

Phases 1 and 2 primarily focus on weight loss through adjustment to a plant-based alkaline diet which helps reduce inflammation. Consumption of milk and milk products, meat, eggs, and poultry are restricted during these phases. In Phase 1, the focus is on a shift from the usual high-carbohydrate unbalanced diet to a balanced diet considering all macro-and micronutrients by increasing the consumption of cooked and raw vegetables along with green smoothies, providing a rich variety of antioxidants and phytonutrients. The reported average calorie intake for Indian T2D patients is 1547 kcal (95% CI 1486 to 1608) and constitutes 64% of the total energy intake [22]. The average calorie intake for Phase 1 is reduced to 1200–1400 kcal/day. In the second phase, one month of intermittent fasting and juice fasting is recommended to aid in faster weight loss and detoxification [23], depending on the BMI of the participant; those already achieving a normal BMI (<23 kg/m^2^) do not undergo intermittent fasting but only juice fasting. The intermittent fasting and juice fasting protocols are described in Fig 3. The average calorie intake during this period ranges from 300–500 kcal on days of juice fasting to 400–500 kcal on single-meal days; the average intake is 800–1000 kcal for days when two meals are consumed. The recipes for juices used in juice fasting (red, white, and green) have been previously described [24]. During periods of fasting, the participants are instructed to closely monitor and report their sugar levels to their assigned physician through a mobile application and accordingly, drug-dose adjustments are done.

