**Fig 3 pone.0306394.g003:**
[figure not shown]
Intermittent fasting protocol: 3, all three meals; 2, Brunch/Lunch and Dinner; 1, Brunch/Lunch or Dinner; 1(D), Dinner only; JF, Juice fasting.

Once the target BMI (based on the initial goal setting-23-25 kg/m^2^ or a 3–5 point drop) is achieved, calorie intake is gradually increased to 1400–1600 kcal to facilitate muscle building in Phase 3. In addition, protein intake is increased to 75–80 grams depending on the intensity of the recommended exercises. The focus here is on building up muscle mass and increasing stamina. The last phase emphasises on maintenance diet. In this phase, once the blood sugar levels have stabilised, other food items restricted from the regular diet are reintroduced phase-wise under the close supervision of the dietitian. This helps participants to understand the portion and frequency control required to sustain the results. This phase also helps participants maintain good glycemic control despite the reintroduction of restricted foods. Based on the chosen long-term exercise plan, calorie intake may be increased to 1600–1800 kcal/d (for those who no longer need to lose further weight). This phase is designed to enable individuals to effectively manage their diet and sustain an exercise plan for better glycemic control, while maintaining weight loss post-intervention without support.

During each phase, the blood sugar levels are closely monitored.

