### Outcome measures

The primary outcome measures are a) Weight loss of more than or equal to 10% and b) Remission of T2D (HbA1c less than 6.5% for at least 3 months without medication). Secondary outcomes include a) reduction in dosage and/ or frequency/ class of drug or complete stoppage of diabetes medication, b) improved glycemic control (HbA1c less than 7% with or without medication), c) reduction in fasting glucose levels (below 126 mg/dl) and PP blood glucose levels (below 200 mg/dl) with or without glucose-lowering medications), d) improvement in diabetes-related complications (nephropathy- improvement in terms of eGFR>90 mL/min/1.73m^2^), e) improvement in comorbidities (hypertension- blood pressure ≤140/90 and dyslipidaemia- Total cholesterol <200 mg/dl, triglycerides <150 mg/dl, and HDL >40 mg/dl for males and >50 mg/dl for females), and f) improvement in mental health outcomes (anxiety and depression- Reduction in the score—below 10).

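### Nephropathy improvement is defined as eGFR above 90 alone, with no baseline condition, no required change and no urine albumin

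*Protocol article*

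**What the plan says.** In the protocol article, Outcome measures, item d of the secondary outcomes covers diabetes-related complications and contains one criterion: "nephropathy- improvement in terms of eGFR>90 mL/min/1.73m^2". It states no baseline eGFR, minimum change, confirmatory value or albumin component.

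Other sections bear on this:

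- **Specific objectives** lists two separate targets: "diabetes-related complications (nephropathy), and biochemical parameters (serum lipids, liver function tests, and kidney function tests". The complication is thus named apart from the kidney function tests.
- **Setting and eligibility criteria, Table 1** excludes "Advanced complications related to nephropathy (eGFR<30 mL/min/1.73 m^2^, urine microalbumin >1000 mg". Entrants can therefore have eGFR from 30 to above 90, with albuminuria up to that limit.
- **Biochemical** includes "serum creatinine levels, eGFR, urine microalbumin, liver function parameters" in the secondary tests, which "will be collected based on availability in the submitted reports".
- **Dietary modifications** says of Phases 1 and 2: "Consumption of milk and milk products, meat, eggs, and poultry are restricted during these phases". Of Phase 3, after a rise in protein to 75–80 g, it says: "The focus here is on building up muscle mass and increasing stamina". In the last phase, restricted foods are reintroduced.
- **Discussion** (limitations) acknowledges that the trial is not truly randomised.

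**The concern.** The criterion describes a state at follow-up but is labelled an improvement. In a randomised trial, the share of participants already above the cut-off would balance on average. Here the groups come from different clinics, so that share may differ at entry, and the difference would pass straight into the result.

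The criterion also leaves out albuminuria, the other marker the protocol uses to recognise advanced nephropathy. And because it is a single cut-off, it credits very small movements near 90 and ignores large ones below it.

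This is the only outcome addressing complications, and the abstract's discussion presents the study as showing effectiveness in the management of T2D and its complications. A criterion that can be met without change, and missed despite real change, supports that claim poorly.

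**Working it through.** The article gives no event rate, power or sample size for this outcome, so there is no stated figure to reproduce. Two checks apply.

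**1. Apply the definition to participants whom Table 1 admits.** This uses only the text.

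| Course from baseline to follow-up | Change in eGFR | Meets eGFR >90? |
|---|---|---|
| Albuminuria, eGFR 95, nothing changes | 0 | Yes |
| Albuminuria normalises, eGFR stays at 75 | 0 | No |
| eGFR 45 to 70 | 70 − 45 = +25 | No |
| eGFR 89 to 91 | 91 − 89 = +2 | Yes |

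Suppose nobody's eGFR changes, and let p_I and p_C be the proportions entering above 90 in the intervention and control groups. The apparent effect is then p_I − p_C, which is purely a baseline difference. With 180 per group, each extra participant who starts above 90 adds 1/180 = 0.56 percentage points.

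**2. How far must creatinine move to cross 90?** The article names no eGFR equation. Assume eGFR is proportional to creatinine^(−b), with b from 1.0 to 1.2. The fractional fall in creatinine needed from baseline eGFR E is

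1 − (E/90)^(1/b).

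For example, at E = 85 and b = 1.0: 1 − 85/90 = 5.6%.

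| Baseline eGFR | Fall needed, b = 1.2 | Fall needed, b = 1.0 |
|---|---|---|
| 89 | 0.9% | 1.1% |
| 87 | 2.8% | 3.3% |
| 85 | 4.7% | 5.6% |
| 80 | 9.3% | 11.1% |
| 75 | 14.1% | 16.7% |
| 60 | 28.7% | 33.3% |
| 45 | 43.9% | 50.0% |
| 30 | 60.0% | 66.7% |

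The 2021 CKD-EPI creatinine equation, also an assumption, puts these in absolute terms for ages 30–70. Going from 85 to 90 needs a fall of about 0.044–0.055 mg/dl in men and 0.035–0.043 mg/dl in women. Going from 80 to 90 needs about 0.07–0.12 mg/dl. Under the same equation, a man of 55 moves from 88.9 at 1.00 mg/dl to 91.1 at 0.98 mg/dl, a 2% fall.

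The cut-off is therefore sensitive for baselines of about 80–89. It is not sensitive at 60 or below, where it fails the other way by ignoring gains.

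**The case against.** The strongest reply has five parts.

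- **Any cut-off is fragile near its edge.** True, and the second table shows that the fragility fades quickly below 80. The article gives no baseline eGFR distribution, so the number affected is unknown. The first check does not depend on this.
- **The diet and muscle mechanism is not demonstrated.** A reader might infer that the intervention would push eGFR above 90 through lower creatinine. The documents do not support that. They give no creatinine response and no eGFR equation. The meat restriction belongs to Phases 1 and 2; later phases raise protein, build muscle and reintroduce restricted foods. Less meat would lower creatinine and more muscle would raise it, so the net direction at 12 months is open.
- **Albuminuria may still be analysed.** It is on the laboratory list, and the objectives mention kidney function tests. Its absence from this definition does not show that it will be ignored. Table 1 also uses it only to exclude advanced disease and does not define nephropathy.
- **Improvement may be meant to apply only to those at or below 90 at entry, and Statistical analyses allows for baseline adjustment.** That adjustment is worded as something that may be considered, and no such restriction is written. Even with it, a participant with albuminuria and eGFR 95 drops out of the outcome, and 45 to 70 still does not count.
- **Albuminuria data may be sparse.** This stands. It is a good reason not to make albuminuria the sole criterion.

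Two further inferences also fail. A fall in eGFR from a high value would not be read as harm: the outcome has no worsening category, and 120 to 95 still satisfies it. Nor can it be said that many older participants could never meet the criterion, because no baseline distribution is given.

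**Conclusion.** The concern holds for the definition as written. From the text alone, eGFR >90 can be met with no change, misses a 25-point gain below 90, and cannot register albuminuria regression. In non-randomised groups it can also turn a baseline difference into an apparent effect.

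The threshold sensitivity, a creatinine fall of roughly 1–11% from baselines of about 80–89, rests on the assumption of a creatinine-based equation with exponent 1.0–1.2. That diet or muscle change in the intervention group contributes is plausible but inferred, and its direction is unknown.

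The point should be corrected, but its reach is limited. This is one secondary outcome, and neither the sample size nor the primary analysis is affected.

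**What to change.** Amend item d of the secondary outcomes as follows:

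1. Replace the bare cut-off with the between-group difference in continuous eGFR change from baseline to 12 months, adjusted for baseline eGFR.
2. Add regression of albuminuria category at 12 months among participants with raised urine albumin at baseline.
3. If eGFR >90 is kept, report it only among participants at or below 90 at baseline, as a supporting result.
4. State that creatinine-based eGFR can move with diet and muscle mass.

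The cost is an amendment to one outcome definition, using measures already on the laboratory list. The downside is that the albuminuria analysis rests on a subset of unknown size, because secondary tests are taken only where submitted reports contain them, and availability could differ between clinics. Microalbumin should therefore be requested at baseline and 12 months where possible, and the number with paired values reported by group.

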### Statistical analyses

Primary outcome measures will be analysed using two-sided statistical tests with a type I error rate of α = 0.05. Primary analysis will be performed using the intention-to-treat method. Categorical data will be compared between the two groups using chi-square or Fisher’s exact tests. Continuous data will be evaluated using parametric or non-parametric tests based on data distribution.

For outliers (± 3 standard deviation), efforts will be made to cross-check and obtain the correct values. Failing this, the case will be considered as missing data. In the case of random missing values, two separate analyses will be performed: one including the cases with missing data by choosing pairwise deletion and the other excluding it using listwise or case-wise deletion. A complete case analysis will be considered if differences are observed between the two analyses. In the case of non-random missing values, the imputation method may be used by replacing the missing value with the mean for that variable.

Potential adjustments for baseline values, age, gender, and disease duration may be considered. Multivariable linear and logistic regression analyses will be used to determine predictors of remission. Finally, subgroup analyses may be performed based on factors such as gender, age, comorbidity, diagnosis length, and severity to investigate potential variations in treatment responses.

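### The only listed lipid outcome is a yes/no target rule without LDL; the serum-lipids objective has no matching outcome and should get a baseline-adjusted analysis of each fraction

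*Protocol article*

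**What the plan says.** All references are to the protocol article.

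- **Outcome measures.** Secondary outcome (e) is "improvement in comorbidities", and its lipid part reads "dyslipidaemia- Total cholesterol <200 mg/dl, triglycerides <150 mg/dl, and HDL >40 mg/dl for males and >50 mg/dl for females". It is the only lipid item in that section. It describes a state to be reached, with no change from baseline and no LDL term.
- **Biochemical.** The secondary tests include "lipid profile (total cholesterol, HDL, LDL, and VLDL"; the secondary tests "will be collected based on availability in the submitted reports".
- **Specific objectives.** The secondary objective covers "comorbidities (hypertension and dyslipidaemia" and, as a separate item, "biochemical parameters (serum lipids, liver function tests, and kidney function tests". The second item has no counterpart in Outcome measures.
- **Statistical analyses.** "Categorical data will be compared between the two groups using chi-square" or Fisher's exact tests; continuous data get a parametric or non-parametric test. Adjustment for baseline values, age, gender and disease duration is left optional.
- **Design and Discussion.** The trial is open-label with a matched control group drawn from other clinics. The authors say that it is not a true randomised trial.

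**The concern.** The dyslipidaemia outcome turns a lipid panel into one yes/no answer and leaves out a fraction that the trial already extracts. If the three limbs form one composite, HDL acts as a veto: a large fall in LDL counts for nothing when HDL stays at or below its cut-off. In the other direction, LDL can go up in a participant who is scored as improved.

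Two features make this more than a matter of taste. The objectives promise an answer on serum lipids, and no listed outcome gives one. Also, the groups are not randomised, so baseline lipids may differ between the programme and the control clinics. An unadjusted comparison of the percentage at target would carry such a difference straight into the result.

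**Working it through.** The plan states no power, sample size or alpha for this outcome, so there is no figure to reproduce. The check has three steps.

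**1. What the rule allows.** Inputs from Outcome measures: total cholesterol (TC) < 200, triglycerides (TG) < 150, HDL > 40 (men) or > 50 (women), all mg/dl. Using the fractions listed under Biochemical, TC = HDL + LDL + VLDL, so a participant at target must have

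LDL < 200 − HDL − VLDL.

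| | VLDL 15 | VLDL 30 |
|---|---|---|
| Man, HDL 41 | 200 − 41 − 15 = 144 | 200 − 41 − 30 = 129 |
| Woman, HDL 51 | 200 − 51 − 15 = 134 | 200 − 51 − 30 = 119 |

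TC therefore caps LDL but does not fix it.

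**2. Worked cases.** The values are illustrative, and VLDL = TG/5 is assumed.

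| | HDL | LDL | VLDL | TC | TG | At target? |
|---|---|---|---|---|---|---|
| Woman, baseline | 46 | 168 | 36 | 250 | 180 | No |
| Woman, 12 months | 47 | 91 | 22 | 160 | 110 | No, on HDL alone |
| Man, baseline | 38 | 100 | 40 | 178 | 200 | No, on TG and HDL |
| Man, 12 months | 45 | 125 | 28 | 198 | 140 | Yes |

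The woman's LDL falls by 168 − 91 = 77 and she is not improved. The man's LDL rises by 125 − 100 = 25 and he is improved. His non-HDL cholesterol also rises, from 178 − 38 = 140 to 198 − 45 = 153.

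**3. Information lost, as a range.** Simulation with 126 per group (180 × 0.7, from the planned 180 and 30% dropout). Every lipid value is an assumption: LDL mean 115, SD 32; HDL mean 41 (men) and 47 (women), SD 9; 60% men; median TG 150, SD of log TG 0.45; baseline to follow-up correlation 0.6. The composite is compared by chi-square and LDL by analysis of covariance on its baseline value, both at the 5% level.

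| Assumed effect of the programme | Power, composite | Power, adjusted LDL |
|---|---|---|
| LDL −13, TG −10%, HDL −2 | about 0.1 | about 0.98 |
| LDL −13, TG −10%, HDL 0 | 0.27 (about 22% v 15%) | 0.98 |
| LDL −13, TG −20%, HDL 0 | 0.56 | about 0.98 |
| LDL −13, TG −20%, HDL +3 | 0.90 | about 0.98 |
| LDL −6, TG −10%, HDL 0 | 0.18 | 0.44 |
| LDL 0, TG −20%, HDL +2 | about 0.5 | 0.05 |

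With 80 per group, the second row becomes about 0.2 against 0.88. The last row shows that LDL alone is not a sufficient replacement: where the effect lies in TG and HDL, the composite sees it and LDL does not. This argues for all the fractions, not for LDL in place of the rule.

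**The case against.** The strongest reply is that serum lipids are already a separate secondary objective, that LDL is on the collection list, and that the analysis section provides for continuous data and permits baseline adjustment. The list of secondary outcomes need not be exhaustive, and an article may leave the detail to a fuller document. Much of this stands. A reader might infer that the trial will miss an LDL benefit or cannot report one; the documents do not support that. What remains is that the only lipid outcome actually written down is the cut-off rule, and that baseline adjustment is optional in a non-randomised comparison.

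Other limits also stand:

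- TC < 200 restrains LDL, and more tightly as triglycerides approach their cut-off. At TG 140 (VLDL 28), a man with HDL 41 must have LDL below 131.
- A rise in LDL does not by itself make the label wrong. A man going from HDL 39, LDL 126, VLDL 45 to HDL 41, LDL 139, VLDL 15 has LDL up 13, yet non-HDL cholesterol falls from 171 to 154.
- Counting improved participants whose LDL lies above baseline would not measure misclassification. Within-person variation alone produces many such rises, even when mean LDL truly falls.
- A reader might take one row of the power table as the size of the loss. No figure in the documents favours any row, and the trial claims power only for weight and HbA1c.
- The wording could mean three separate criteria. The HDL veto would then weaken, but LDL would still be absent.

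Which fractions should define clinical improvement is a choice of target and is not judged here.

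**Conclusion.** The point holds as a cheap improvement to one secondary outcome; the primary outcomes are untouched. It is certain from the text that the listed lipid outcome is a target state without LDL, that LDL is to be collected, and that the serum-lipids objective has no listed outcome. It follows by arithmetic, if the limbs form one composite, that a large LDL fall can be scored as no improvement on HDL alone. That LDL can rise in a participant scored as improved, within the room left by total cholesterol, follows on either reading.

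The cost in power is not determined: from severe to slight for an LDL fall of 13 mg/dl, and reversed if the programme acts on triglycerides and HDL only. The case for change therefore rests on answering the stated objective, and on baseline adjustment where groups are not randomised. It does not rest on any single power figure, nor on a claim that the cut-offs are the wrong ones.

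**What to change.** - Under the serum-lipids objective, specify as the secondary lipid analysis the between-group difference at 12 months in total cholesterol, LDL, triglycerides and HDL, each adjusted for its own baseline value. Make that adjustment fixed, not optional.
- Keep the cut-off rule in outcome (e) as a supporting percentage, and state whether its three limbs form one composite or three separate criteria.
- Name triglycerides in the lipid profile under Biochemical. The rule needs them and that list does not mention them.
- Report how many participants in each group have each fraction at both time points.

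The cost is wording in the protocol or analysis plan. There will be four secondary comparisons instead of one, to be labelled as secondary. LDL will be available only where the submitted reports include it, a condition that applies equally to total cholesterol and HDL. No new lipid cut-off is needed.

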#### Mental health assessment

The validated Patient Health Questionnaire (PHQ-9) and Generalised Anxiety Disorder (GAD-7) scale will be used to assess the prevalence of depression and anxiety, respectively.

The PHQ-9 is a 9-item self-report screening tool for depression. Each item is rated on a 4-point scale from 0 to 3 (0 = never, 1 = several days, 2 = more than half the time, and 3 = nearly every day). The overall scores range from 0 to 27, with higher scores indicating greater symptom severity. Scores 5, 10, 15, and 20 represent cut-offs for mild, moderate, moderately severe, and severe depression, respectively. The PHQ-9 has a sensitivity of 88% and a specificity of 88% for detecting depression [20].

The GAD-7 is a 7-item self-report screening tool for anxiety. Each item is rated on a 4-point scale from 0 to 3 (0 = never, 1 = several days, 2 = more than half the time, and 3 = nearly every day). The overall scores range from 0 to 21, with higher scores indicating greater symptom severity. Scores 5, 10, and 15 represent cut-offs for mild, moderate, and severe anxiety, respectively. The GAD-7 has a sensitivity of 89% and a specificity of 82% for detecting anxiety [21].

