#### Psychological support

The third protocol of psychological intervention is designed to address stress and anxiety levels by raising awareness of the mind-body connection. At baseline, all participants will be assessed for depression and anxiety using validated tools: the Participant Health Questionnaire (PHQ) and Generalised Anxiety Disorder (GAD) scale. Those who exhibit moderate to severe anxiety and/or depression are referred to in-house psychologists for one-on-one counseling sessions tailored to their individual needs. Drawing from a range of therapeutic techniques, including Cognitive Behaviour Therapy (CBT), Rational Emotive Behaviour Therapy (REBT), Neuro-Linguistic Programming (NLP), Clinical Hypnotherapy, Life Coaching, Pranic Healing, and Eclectic Therapy, therapists work to meet the unique needs of each participant.

All participants, regardless of their anxiety and depression scores, attend 56 days of group therapy sessions during the one year; these incorporate guided meditation and journaling. The intervention is centred on cultivating positive energy through principles such as the law of attraction, gratitude, and affirmation [26]. Engaging in cognitive activities, such as creating a vision board, serves as a proactive measure for achieving personal goals and enhancing emotional intelligence [26, 27]. The intervention also emphasises the importance of long-term health management and maintenance through online group sessions following the program.

At the end of 6 months, the PHQ and GAD are re-administered to assess the improvement in the mental health outcomes.

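### The mental-health responder rule (score falling below 10) has no minimum change and sits on the 'moderate' cut-off; as the basis of an unadjusted group comparison it loses information (minor)

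*Protocol article*

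**What the plan says.** Outcome measures in the protocol article lists, as the last secondary outcome (item f), "improvement in mental health outcomes (anxiety and depression- Reduction in the score—below 10". It names no minimum fall.

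Mental health assessment sets the bands. For PHQ-9: "Scores 5, 10, 15, and 20 represent cut-offs for mild, moderate, moderately severe, and severe depression, respectively". For GAD-7: "Scores 5, 10, and 15 represent cut-offs for mild, moderate, and severe anxiety, respectively". Ten is thus the lower edge of 'moderate' on both scales. For measurement quality, that section gives only detection accuracy: "The PHQ-9 has a sensitivity of 88% and a specificity of 88% for detecting depression" and "The GAD-7 has a sensitivity of 89% and a specificity of 82% for detecting anxiety". It gives no re-test reliability, expected mean or SD.

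Statistical analyses assigns categorical outcomes to a chi-square or Fisher's exact test between the two groups. Adjustment for baseline values appears there only as a possibility. The groups come from different clinics and are not randomised against each other (Setting and eligibility criteria; Sampling and recruitment process; limitations paragraph of the Discussion).

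**The concern.** A response threshold placed at the edge of a severity band, with no required amount of change, has two weaknesses.

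- **It ranks changes poorly.** A one-point fall across the line is a success, and a large fall that stops on the line is a failure.
- **It is exposed to regression to the mean.** Participants who score 10 or more once are partly selected on a high reading. Some will read below 10 next time with no change in their condition. The chance depends strongly on how far above 10 they started.

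If the percentage improved carries the group comparison through an unadjusted test, noise dilutes any real effect. If the clinics differ enough in baseline severity, part of the observed difference could reflect case mix. Mental health is a named secondary objective and psychological support is one of the four intervention components, so the result is likely to be reported and read.

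**Working it through.** The article states no rate, SD or power for this outcome, so there is no figure to reproduce. The check has four steps.

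**1. The rule against the article's own bands.**

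| PHQ-9 change | Bands | Fall | Improved under the rule? |
|---|---|---|---|
| 10 to 9 | moderate to mild | 1 point | yes |
| 22 to 10 | severe to moderate (two bands) | 12 points | no |

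**2. Re-test noise with no true change (illustration; all inputs assumed).** Each participant has a stable true score drawn from a gamma distribution. Each visit adds independent normal error with SD = SD × √(1 − reliability). Scores are rounded and limited to 0–27, with 2,000,000 participants per scenario. The error SD runs from 4.5 × √0.1 = 1.4 to 5 × √0.3 = 2.7 points. The share of participants at 10 or more at baseline who score below 10 on re-test is:

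| Reliability | Mean/SD 5/4.5 | Mean/SD 7/5 | Difference (points) |
|---|---|---|---|
| 0.7 | 37.2% | 34.7% | 2.5 |
| 0.8 | 28.7% | 27.6% | 1.1 |
| 0.9 | 19.4% | 18.9% | 0.5 |

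Repeat runs move these by a few tenths of a point. By starting score, the rate is 27–47% for baseline 10–14 and 0–9% for baseline 15 or more. Capping at 21, the GAD-7 maximum, makes no material difference.

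**3. Wider assumptions.** A normal model with mean 5–10, SD 4–6 and re-test correlation 0.70–0.94 gives about 10% (mean 10, correlation 0.94) to 50% (mean 5, SD 4, correlation 0.70). A right-skewed model with mean 4–7 and SD 4–5 gives about 18–54%. The 19–37% is therefore one subset of assumptions and not a bound.

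**4. What this does to the group comparison.** At equal reliability, two populations 2 points apart in mean score differ by 0.5 to 2.5 percentage points (last column of the table in step 2). Most of the 19–37% spread comes from the assumed reliability, a property of the questionnaire that both groups share.

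A spurious difference can also be written in terms of case mix. At reliability 0.8 the no-change rates are about 38% for baseline 10–14 and 3% for 15 or more:

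- If the share of cases at 10–14 differs by 10 percentage points: 0.10 × (38 − 3) = 3.5 points.
- If it is 80% in one group and 50% in the other: 0.8 × 38 + 0.2 × 3 = 31.0% against 0.5 × 38 + 0.5 × 3 = 20.5%, a difference of about 10 points.

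The second case needs a large imbalance, and nothing in the article shows that one is expected.

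**The case against.** The strongest reply is that moving below a recognised severity cut-off is an ordinary responder definition, that most of the listed secondary outcomes use thresholds, and that a concurrent control group carries the same re-test noise. That largely stands. With similar baseline scores the noise does not favour either group, and what remains is the usual cost of dichotomising a score. The cut-off is, however, supported in the article only by detection accuracy, which does not show how much change is real.

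A second reply is that the Statistical analyses section already allows baseline adjustment and tests for continuous data, and that details may sit in an analysis plan not shown. This stands in part. The article fixes the responder rule, names an unadjusted test for categorical data and leaves adjustment optional.

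Stronger readings are tempting, and the article does not support them:

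- **That 19–37% of cases will 'improve' by noise.** The article supplies none of the inputs needed for such a rate.
- **That the rule biases the result towards the intervention.** The direction is unknown, and the size is small unless baseline severity differs materially.
- **That the plan uses 10 both as its case definition and as its response line.** Psychological support says "Those who exhibit moderate to severe anxiety and/or depression are referred to in-house psychologists". That is a referral trigger within the intervention, and the outcome is not tied to the referred group.
- **That a minimum fall of 5 points is required.** The figure is not in the article. Under it, 22 to 10 would still fail, 13 to 9 would become a failure, and 2–18% of baseline cases would still respond with no change in the main scenarios.

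**Conclusion.** The point holds in limited form. The responder rule shares its value with the 'moderate' cut-off on both scales and requires no minimum change, so it treats 10 to 9 as success and 22 to 10 as failure. Re-test noise would move a non-trivial share of baseline cases across the line: about 19–37% in the main illustration and about 10–54% under wider assumptions, all resting on assumed means, SDs and reliabilities. The main consequence is dilution and loss of information. A spurious group difference is under about 3 percentage points for a 2-point difference in mean score, and reaches about 10 points only under a marked difference in case mix. Severity is minor: this is one secondary outcome, and the sample size does not rest on it.

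**What to change.** In Outcome measures and Statistical analyses, for PHQ-9 and GAD-7 separately:

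- Make the between-group test a regression of the follow-up score on group and baseline score. It replaces the unadjusted chi-square or Fisher's test for this outcome and makes the baseline adjustment fixed instead of optional.
- Report the percentage moving from 10 or more at baseline to below 10 as a descriptive result.

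A minimum fall may be added to the descriptive figure if the investigators want one, but it is not needed.

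The cost is one regression per scale on data already collected. The downside is that the responder percentage no longer carries the formal test. Adjustment also does not remove all baseline imbalance between non-randomised groups. With no true change and group means 2 points apart, the expected leftover is (1 − reliability) × 2, which is 0.2 to 0.6 score points for reliability 0.9 to 0.7. The result should still be read as a non-randomised comparison.
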